#### Concomitant care and interventions

No concomitant medications, care, or intervention are prohibited as long as they do not interfere with the rhythm of CC relay or feedback device (CPRmeter^®^) use. The use of an automatic CC device set up before 5 min of CPR in the protocol is an exclusion criterion. If it is set up after 5 min, the collection of the CC data is restricted to those recorded before.

### Outcomes

#### Primary outcomes

Since this is a factorial-design study, there are two primary outcomes:
The chest compression fraction (CCF) (as a percentage) will be used for the comparison between a 2-min versus 4-min (A vs B) relay of CC. CCF is defined according to Saldanha et al. [30] as a measure of quality of CPR (domain), corresponding to the relative amount of time during which the CC are performed during CPR (specific measurement), formally computed as the ratio of CPR time during which CCs are performed (low-flow) divided by the CPR time performed on the patient by the out-of-hospital resuscitation team. No-flow (no CC performed), low-flow, and CPR times (in seconds) are automatically recorded in real time by the CPRmeter® (metric). The mean CCF will be aggregated for 2 min versus 4 min (A vs B groups) (method of aggregation). The time point of interest for this endpoint is over the duration of CPR (time point).The correct compression score (CCS) (as a percentage) will be used for the comparison between real-time feedback guidance by CPRmeter^®^ versus no real-time feedback guidance by CPRmeter^®^ (C vs D). CCF is defined according to Saldanha et al. [30] as a measure of quality of CPR (domain), corresponding to the percentage of CC for which the depth is correct (50 to 60 mm), the frequency is correct (100 to 120/min), and the relaxation is correct (< 2500 g) (specific measurement). The depth (in millimeters), the frequency (number of compressions per minute), and the release (residual strength in grams) of the CC are automatically recorded in real time by the CPRmeter^®^ (metric). The mean CCS will be aggregated for real-time feedback guidance by CPRmeter^®^ versus no real-time feedback guidance by CPRmeter^®^ (C vs D groups) (method of aggregation). The time point of interest for this endpoint is over the duration of CPR (time point).

#### Secondary outcomes

The secondary outcomes are as follows:
The depth of each CC (in millimeters), recorded continuously by the guidance system (average and percentage correct)The frequency of CC (in number of compressions per minute), recorded continuously by the guidance system (average and percentage correct)The release of the CC, corresponding to the residual force (in grams), recorded continuously by the guidance system (average and percentage correct)The subjective fatigability, assessed by the rescuers who performed CC using the Borg scale (average of the Borg rescuer scale values) [31]Time and length of care (in minutes and seconds) based on the following events: CA time, CC start time, the out-of-hospital resuscitation team’s resuscitation start time, and resuscitation end time (ROSC or death of the patient)The length (in minutes and seconds) of no-flow and low-flow: no-flow and low-flow times prior to the arrival of the out-of-hospital resuscitation team (declarative) and no-flow and low-flow times during resuscitation by the out-of-hospital resuscitation team (measured by the CC guidance device)The rate of return of spontaneous circulation (ROSC)The survival rate at hospital admissionThe value of NSE at admission and day 3 [28]The survival rate on day 1 and day 30 (or resuscitation output if earlier)Cerebral performance category score (CPC) at day 30 or intensive care discharge [29]

The study will be conducted within the framework of the French national network of the RéAC Cardiac Arrest Registry (http://www.registreac.org/).

### Data collection

Data will be collected using international Utstein-style guidelines on reports for OHCA and using the automatic data registration of the CPRmeter^®^ device. Data from the CPRmeter^®^ will be uploaded to the section of the French national network of the RéAC Cardiac Arrest Registry (http://www.registreac.org/) dedicated to the study. All other data will be collected by doctors in charge of the patient and entered into an eCRF of the dedicated section of the RéAC Cardiac Arrest Registry. Clinical research assistants (locally and in the promoting center) will help and monitor the data collection and the eCRF. The data input is checked by computer.

Apart from the CC quality data report by the CPRmeter^®^, data collection will be performed as follows:

#### At day 0

Demographic characteristics: identity, social security number, intervention, street address, age (year), sex (male/female), weight (estimated, in kilograms), height (estimated, in meters)Patient history: medical history (cardiovascular, respiratory, diabetes, end of life, others)History of the disease: presumed etiology of CA (cardiac, neurological, respiratory, asphyxiation, poisoning, drowning, unknown, others), durations of no-flow and low-flow periods before medical resuscitation (minutes), existence of witnesses, resuscitation maneuvers undertaken before the arrival of professional rescuers (CC, defibrillation, ventilation)History of the advanced CPR carried out by the out-of-hospital resuscitation team:
Duration of low-flow, no-flow, and advanced resuscitation (minutes, obtained by CPRmeter^®^ recording)Quality of the CC and its components (frequency in CC per minute, depth in millimeters, and release in grams obtained by the CPRmeter^®^ recording)EtCO_2_ values (mmHg) 1 min (± 20 s) after intubation, the highest obtained during CC (before ROSC) and at the end of resuscitation (1 min ± 20 s after the ROSC or during the decision to end resuscitation) [32, 33]External electrical shocks (number, intensity in joules)Initial rhythm upon the out-of-hospital resuscitation team arrival (asystole, ventricular fibrillation, ventricular tachycardia without pulse, electromechanical dissociation)Numbers and total doses of vasopressor amines and antiarrhythmic administration (milligrams)ROSC or death

Survival at hospital admission

#### At hospital discharge or at day 30

Values of the NSE performed upon the patient’s admission and on day 3 (in micrograms per liter) [28]Survival on day 1 and day 30 (or at the intensive care unit (ICU) discharge if earlier)Length of stay in the ICU (days)Neurological state assessment by the CPC and any sequelae on day 1 and at ICU discharge or on day 30 [29]

### Data management

Trained research staff (clinical research assistants) at each center will collect data using an online national secure database dedicated to cardiac arrest data collection (RéAC; http://www.registreac.org/). The two different eCRF pages for prehospital and intensive care will be completed separately. Data on CC quality from the CPRmeter^®^ will be uploaded with the clinical data from the prehospital period. Deidentified completed data will be sent to the principal investigator at Caen University Hospital. Furthermore, data will be monitored by a data manager. The clinical research manager and two clinical research assistants from the steering committee will be available to help and monitor the data collection and management.

### Data monitoring committee

The data monitoring committee from the national cardiac arrest registry RéAC will ensure the first level of independent data monitoring. A specific-to-the-study data monitoring committee composed of a senior data manager and an assistant data manager (independent from the primary sponsor and the steering committee) will regularly control the maintenance of the informatic system, check the quality of the data entered, and ensure the proper functioning of the automatic data entry control system.

### Safety and potential adverse events

The study implies few changes from OHCA guidelines as real-time feedback is not currently strongly recommended but a possibility, and the time for CPR relay is based on little concrete data [15]. However, feedback tool use has been reported to be safe [20, 34]. In the context of an OHCA, no significant adverse event related to the study is expected. Adverse events can be reported through eCRF, email, and phone calls to the promoter. Serious adverse events will be investigated, and reports will be provided directly to the safety monitoring committee. If they occur, adverse events will be reported in the publication.

### Safety monitoring

A trio of independent experts not involved in the study (safety monitoring committee) will meet when 250 patients have been included to review the monitored data on ROSC and survival on day 0, day 1, and day 30 according to the randomized group. The investigator can request an extra meeting at any time in case of new data in the literature or if an event occurs in the study requiring the safety monitoring committee’s advice.

### Steering committee

A steering committee composed of the principal investigator, a statistician, a clinical research manager, and two clinical research assistants will be in charge of the presentation, the implementation and follow-up of the study at the different participating centers, and the overall management of the study (coordination of the data management team and safety committee).

### Auditing

Research assistants from the steering committee will conduct at least one onsite monitoring visit per year over the course of the study at 100% of the recruiting sites (with repeat visits to sites where performance is a concern). The primary objectives during the onsite visits are to educate, support, and solve problems. At the start of the trial, the monitors will conduct a tutorial on the procedure to extract data from the CPRmeter^®^ and on the online data entry system. The investigators will practice so that the monitors can confirm that the investigators are proficient in all aspects of data extraction and entry.

### Schedule of data collection

Intervention assignment will be performed before starting the trial. If patients survive their CA, they will be followed up for 1 month after enrollment. The schedule of data collection is summarized in Table 2.

**Table 2 Tab2:**
[figure not shown]
Schedule of data collection

### Trial registration

The trial was registered on 28 January 2019 at http://www.clinicaltrials.gov under number NCT03817892 (https://clinicaltrials.gov/ct2/show/NCT03817892?term=[name]&draw=2&rank=1).

### Statistical analyses

The main analysis population will be defined as all randomized patients for whom CPR has been engaged, according to a modified intent-to-treat principle. Randomized patients who do not fulfill the inclusion criteria, die, or have a ROSC at prehospital team arrival will be excluded from the main modified intent-to-treat principle analysis. We plan to conduct a pure intent-to-treat analysis in which these excluded patients and patients with missing data will have their outcome imputed by multiple imputation process. This analysis will test the effect of these exclusions on trial outcomes. The statistical analysis plan will follow the recommendations of the tests with a factorial plan described in the CONSORT statement [35], namely, (i) the verification of the absence of interaction between the 2 interventions tested (here on different criteria of judgment) and (ii) a separate analysis by type of multivariate intervention that will systematically include the effect of the untested intervention. Regarding the main criterion of judgment, the average percentage of CCF for comparison of A versus B and the average percentage of CCS for comparison C versus D, the two groups will be compared in terms of superiority of the 4-min group (B) and the guidance group (D) by a multivariate generalized linear regression model including the randomization group as an explanatory variable as well as the other intervention received as a covariable of the model and possibly the interaction of the 2 interventions if it is significant (Student’s test for independent series).

The other criterion (secondary outcomes) will be compared between the groups using the appropriate tests and in an exploratory manner. For example, the qualitative variables will be compared between the groups with the *χ*^2^ test, the quantitative variables by Student’s *t* test, and the survival by the log-rank test.

All confidence intervals of the parameters to be estimated will be established at 5% risk (95% confidence interval). No interim analysis will be performed for primary outcomes (CCF and CCS). The significance level is set at 0.05. The analysis will be performed in SAS software v9.4 (SAS Institute NC, Cary).

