### Trial interventions

CA, matching the eligible criteria, managed by an out-of-hospital resuscitation team can be included according to a procedure of immediate vital emergency (article L1122-1-3 of the Code of Public Health) [27]. The randomization is performed by the out-of-hospital resuscitation team’s doctor during the transportation on the spot to know the randomization arm before the arrival at the place of the intervention. The patient is randomized using the online centralized 24/7 server or the backup sealed opaque “off-grid area” emergency randomization envelopes as described in the “Randomization, allocation” section above.

For all groups, the CPRmeter^®^ CC guidance system was positioned on the patient’s chest with a disposable adhesive. The CPRmeter^®^ is always on for all groups. (1) In the CC guidance situation by the CPRmeter^®^ (group D), rescuers have onscreen real-time visual feedback on the quality of the CC performed and indications of corrections to improve the quality, if necessary. (2) In cases of nonguidance of the CC by the CPRmeter^®^ (blind), a specific screen cap is set up on the screen to hide the feedback in the unguided group (group C). The CPRmeter^®^ is always on to record the CC quality data.

The duration or rhythm of a relay is the time during which a rescuer performs a CC before being relayed by another rescuer. This time is 2 min in group A according to the guidelines in effect and 4 min in group B, which is the experimental group.

The CPR of OHCA is therefore normally undertaken according to the guidelines in effect by the out-of-hospital resuscitation team, except for the relay rhythm in group B, which is 4 min. Due to the 2 × 2 factorial design, four situations are possible (Fig. 1):
CC unguided + relay between 2 rescuers switching at 2 min (C + A)CC unguided + relay between 2 rescuers switching at 4 min (C + B)CC guided + relay between 2 rescuers switching at 2 min (D + A)CC guided + relay between 2 rescuers switching at 4 min (D + B)

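### The pure intent-to-treat sensitivity analysis imputes CCF and CCS for patients who had no CPR from the team, in whom both are undefined rather than missing, so for them it is neither a true ITT nor a test of the exclusions

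*Protocol article*

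**What the plan says.** All references are to the protocol article.

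- **Main population (Statistical analyses).** The main analysis covers "all randomized patients for whom CPR has been engaged, according to a modified intent-to-treat principle". Randomised patients who fail the inclusion criteria are left out, and those who "die, or have a ROSC at prehospital team arrival will be excluded from the main modified intent-to-treat principle analysis".
- **Sensitivity analysis (same section).** A pure intent-to-treat analysis is planned in which "these excluded patients and patients with missing data will have their outcome imputed by multiple imputation process". Its purpose is stated: "This analysis will test the effect of these exclusions on trial outcomes". The imputation model is not described.
- **CCF (Primary outcomes).** Time with compressions is "divided by the CPR time performed on the patient by the out-of-hospital resuscitation team".
- **CCS (Primary outcomes).** This is the "percentage of CC for which the depth is correct (50 to 60 mm"), with rate and release also on target.
- **Time frame.** For both outcomes, "The time point of interest for this endpoint is over the duration of CPR".
- **Timing of randomisation (Trial interventions).** The team doctor randomises on the way to the patient, "to know the randomization arm before the arrival at the place of the intervention". The Blinding section says that care providers are not blinded.

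**The concern.** Multiple imputation is meant for a value that exists but was not observed. A patient who gets no CPR from the team has no CCF and no CCS to observe. Putting a number there changes the question to what compression quality would have been had the team given CPR. The article does not pose that question or say why it matters.

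The stated purpose of the analysis is also at stake. The team knows the arm before it decides whether CPR is engaged, and one noninclusion criterion is the medical team's own decision not to resuscitate. Exclusion after randomisation could therefore differ between arms. The pure ITT analysis is the only check on this that the article describes. If it cannot detect the problem, its agreement with the main result would reassure without cause.

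**Working it through.** **1. The definitions side by side.** For a patient with no team CPR:

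- CCF = low-flow time during team CPR / team CPR time = 0/0.
- CCS = 100 × correct compressions / all compressions = 0/0.

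Both are undefined. The article assigns these patients no other value.

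**2. The plan's own figures, used as simulation inputs.** The Determination of sample size section gives, for CCF, 70% against 75%, SD 17, two-sided alpha 5% and power 90%. With n = 2(1.960 + 1.282)² × SD²/difference²:

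- CCF: 2 × 10.51 × 17²/5² = 242.9, so 243 per group. This matches the article.
- CCS (difference 15, SD 36): 2 × 10.51 × 36²/15² = 121.1, so 122 per group. This also matches.

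The point does not depend on these figures.

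**3. Imputation on the randomised factors only.** Let X hold the intercept and the two factors, o the patients with an outcome, m those without, and b the regression estimate in o. Then X_o'y_o = X_o'X_o b, and the imputed values have mean X_m b. Averaged over imputations, the estimate from the completed data is

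(X'X)⁻¹(X_o'X_o b + X_m'X_m b) = b.

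This is the modified ITT estimate, whatever decided who was excluded.

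Simulation: 1,000 trials of 500 patients, 20 imputations, Rubin's rules, exclusion unrelated to arm. The article does not give the share without an outcome; 5% to 30% is an assumption.

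| Share without outcome | Modified ITT effect (SE) | Imputed effect (SE) | Correlation |
|---|---|---|---|
| 5% | 5.035 (1.557) | 5.037 (1.559) | 0.999 |
| 10% | 5.032 (1.602) | 5.028 (1.607) | 0.998 |
| 20% | 4.985 (1.700) | 4.980 (1.708) | 0.995 |
| 30% | 4.973 (1.819) | 4.973 (1.832) | 0.993 |

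The mean difference is below 0.01 points in every row. What remains is imputation noise (SD of the difference 0.08 to 0.22).

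**4. Arm-related exclusion.** This is the situation that the check is meant to detect. All inputs except N = 500, effect 5 and SD 17 are assumptions.

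| Assumed exclusion | Modified ITT | Imputed, factors only | Imputed, with covariate |
|---|---|---|---|
| About 20%, by arm and a prognostic covariate | 7.4 | 7.4 | 4.9 |
| About 19%, by arm and a covariate with outcome correlation 0.5 | 6.37 | 6.38 | 4.87 |
| About 10% in A and 30% in B, poorer prognosis removed more often from B | 7.9 | 7.9 | – |
| The same, with a covariate only weakly related to prognosis | 7.8 | – | 7.4 |

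In variants of the second row, with correlations of 0.3 to 0.7 and 19% to 22% excluded, modified ITT gave 5.8 to 9.1 and imputation with the covariate 4.9 to 5.1.

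A factors-only model thus reproduces the bias. A model holding the covariate that drives exclusion removes it, and a weak covariate removes little. The last column approaches 5 only because the simulation gave every excluded patient an outcome. Patients without team CPR have none.

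**The case against.** **The imputation model belongs to the analysis plan, which is not shown.** This stands. A reader might infer that the pure ITT must always agree with the modified ITT. The article does not support that. The Data collection section lists age, presumed cause, witnesses, earlier no-flow and low-flow times, and initial rhythm. A model using such variables can move the estimate, as step 4 shows. The near-perfect correlations in step 3 describe a factors-only model, not a model that the article has fixed.

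**The sentence also covers patients for whom imputation or analysis is sound.** This stands too. Where team CPR took place but the device record was lost, imputation is appropriate. The Exclusion criteria section shows that some patients found ineligible late did receive CPR, so their values exist. Only patients without team CPR are affected.

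**The word outcome is not tied to CCF and CCS.** True, but the sentence stands in the account of the main analysis, so the primary outcomes are the natural reading. ROSC and survival would not be undefined.

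**The Trial interventions section describes CCF more loosely, over the whole rescue time.** On that wording a patient without compressions might be given a CCF of 0. That would be a known value, again not one to impute, and CCS would stay undefined.

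**It is only a sensitivity analysis.** Correct. A reader might infer that the primary result is biased or invalid. The article does not support this: it gives no exclusion counts, and death or ROSC at arrival precedes the team's intervention, so the arm cannot cause it. The modified ITT may well be defensible. The planned imputation is simply not what would show it.

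None of this answers the core point. The article does not leave the matter open: it fixes imputation for the excluded patients and says what the result will show.

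**Conclusion.** The point holds for randomised patients with no team CPR, reading the imputed outcome as CCF and CCS. Their values are undefined, so the analysis that includes them is not a true ITT. It estimates a hypothetical effect that the article does not define.

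Whether it reveals anything about the exclusions depends on the unstated imputation model. With only the randomised factors it cannot reveal arm-related exclusion: the mean difference was below 0.01 points at an assumed 5% to 30% without outcome, and an assumed bias of about 2 to 3 points passed through unchanged. With strong prognostic covariates the estimate can move, but these patients still gain no real CCF or CCS.

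This deserves correction before analysis. Its reach is limited to a sensitivity analysis, and the main estimate and the sample size do not rest on it.

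**What to change.** 1. Restrict multiple imputation of CCF and CCS to patients in whom team CPR was engaged but the CPRmeter record is missing or incomplete. Include recorded prognostic covariates in the model.
2. For those imputed values, add a delta-shift analysis: move them by arm until the conclusion changes, and report the shift needed.
3. Use the observed values of late-found ineligible patients who did receive team CPR.
4. Report patients without team CPR by randomised arm and reason, with the difference between arms and its confidence interval. This examines arm-related exclusion directly.
5. Compare ROSC and survival, which are defined for everyone, in all randomised patients. First confirm that they are recorded for excluded patients and after a switch to an automated device, since the Trial interventions section stops secondary data collection at that switch.
6. Do not describe imputed CCF or CCS for patients without team CPR as intent-to-treat or as a test of the exclusions.

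The cost is revised wording and a little more analysis work. Items 1 to 4 should need no new measurements, provided the reason for exclusion is recorded.

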## Methods

### Study design and settings

We propose a randomized, multicenter, open-label study using a 2 × 2 factorial design (Protocol CILICA-HS version 4, June 26, 2019) comparing (i) the rhythm of CC relays every 4 min versus every 2 min on the CCF and (ii) the use of real-time guidance of the CC via a guidance tool (CPRmeter^®^) versus no guidance on the quality of the CC (correct compression score). Emergency prehospital services (Service Mobile d’Urgences et de Réanimation) from 12 hospitals in France will participate. The design of the study is summarized in Fig. 1.

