### Randomization, allocation

The block randomization, stratified by trial centers, is performed using a randomization list from a centralized secure online server (internet) 24/7. A backup solution with sealed opaque envelopes will be available in each vehicle participating in the study for situations that do not allow access to the secure randomization server (off-grid area, connection difficulty). There is a stratification of the draw at each center in a 1:1:1:1 distribution: (A + C) 2 min blind, (A + D) 2 min with guidance, (B + C) 4 min blind, and (B + D) 4 min with guidance (Fig. 1).

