### Determination of sample size

We estimated the calculation of the number of subjects required in this trial using a factorial design for the comparison of 2 min versus 4 min (A vs B) on the average percentage of CCS.

With an average CCF of 70% [36] in the control group (group A, 2 min) and a 5% improvement in the experimental group (group B, 4 min), a power of 90%, a two-tailed alpha risk of 5% bilateral, and a standard deviation of ± 17%, 243 subjects per group are required to compare the effect of 2 min versus 4 min (A vs B) on the average percentage of CCF.

Regarding the guiding hypothesis, with a difference of 15% in the CCS between the guided group (D) and the blinded group (C), a standard deviation of ± 36% (12), alpha 5%, and beta 10%, the number of subjects needed is lower (122 per group).

We plan to include 500 patients according to the sample size needed for hypothesis A vs B (243 per group), which is higher than that needed for hypothesis C vs D (122 per group).

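### Randomisation is stratified by centre but the listed primary model omits centre; adding it is a nearly free improvement with a modest gain

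*Protocol article*

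**What the plan says.** Under Randomization, allocation, the protocol article states: "The block randomization, stratified by trial centers, is performed using a randomization list from a centralized secure online server". It adds: "There is a stratification of the draw at each center in a 1:1:1:1 distribution". Each factor of the 2 × 2 design is therefore balanced 1:1 within a centre, up to incomplete blocks. Study design and settings gives the number of strata: emergency services "from 12 hospitals in France will participate".

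Statistical analyses then describes the primary model for each outcome as a generalized linear regression "including the randomization group as an explanatory variable as well as the other intervention received as a covariable of the model". One further term is conditional, namely the product of the two factors, which enters only if it reaches significance. The sentence ends with a bracketed reference to an unpaired Student test. Centre is not mentioned anywhere in that section.

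Determination of sample size uses an ordinary two-group comparison of means with "a two-tailed alpha risk of 5% bilateral" and has no centre term.

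**The concern.** Stratified blocks balance the arms within each centre, so differences between centres largely cancel out of the treatment contrast. A model without centre does not use this. The between-centre variance stays in the residual, and the reported standard error is computed as if centre differences still added noise to the contrast.

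Both primary outcomes measure how rescuers perform compressions, and rescuers belong to hospital services. Some variation between centres is therefore plausible, though the article does not quantify it. If it exists, confidence intervals are wider than they need be, the test rejects less often than its nominal 5% under the null, and some of the precision bought by stratifying is not used.

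**Working it through.** **Inputs from the article.** CCF: difference 5 points, SD 17. CCS: difference 15 points, SD 36. Two-sided alpha 0.05, power 90%, 500 patients (250 per margin), 12 centres.

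**Inputs assumed.** ICC, the between-centre share of outcome variance, from 0 to 0.20. Block size 4 in the simulation.

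**Step 1: the plan's own figures.** n per group = 2 (1.960 + 1.282)² SD² / d².
- CCF: 2 × 10.507 × 289 / 25 = 242.9, so 243, as stated.
- CCS: 2 × 10.507 × 1296 / 225 = 121.04, so 122, as stated.

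With 250 per margin the CCF standard error is 17 × √(2/250) = 1.521, and power is Φ(5/1.521 − 1.960) = 90.8%.

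**Step 2: effect of omitting centre.** With arms balanced within centre:
- true SE, which is also the SE with centre in the model: 1.521 × √(1 − ICC)
- SE reported without centre: about 1.521, so the ratio is 1/√(1 − ICC)
- true type I error without centre: 2[1 − Φ(1.960/√(1 − ICC))]
- power without centre: Φ[(5/1.521 − 1.960)/√(1 − ICC)]
- power with centre: Φ[5/(1.521 √(1 − ICC)) − 1.960]

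Example at ICC 0.10, where √0.90 = 0.949. The SE with centre is 1.442 and the excess is 5.4%. Type I error is 2[1 − Φ(2.066)] = 3.9%. Power is Φ(1.400) = 91.9% without centre and Φ(1.506) = 93.4% with it.

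| Assumed ICC | SE with centre | SE excess without | Type I error without | CCF power without | CCF power with | Difference (points) |
|---|---|---|---|---|---|---|
| 0 | 1.521 | 0% | 5.0% | 90.80% | 90.80% | 0 |
| 0.01 | 1.513 | 0.5% | 4.9% | 90.91% | 91.07% | 0.2 |
| 0.02 | 1.505 | 1.0% | 4.8% | 91.02% | 91.34% | 0.3 |
| 0.05 | 1.482 | 2.6% | 4.4% | 91.35% | 92.13% | 0.8 |
| 0.10 | 1.442 | 5.4% | 3.9% | 91.93% | 93.40% | 1.5 |
| 0.20 | 1.360 | 11.8% | 2.8% | 93.12% | 95.70% | 2.6 |

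**Step 3: CCS.** The SE is 36 × √(2/250) = 3.220. Power at ICC 0 is Φ(15/3.220 − 1.960) = 99.65%, and it rises with ICC under either model. What changes is interval width. At ICC 0.10 the 95% half-width is 1.96 × 3.220 = 6.31 points without centre and 6.31 × 0.949 = 5.99 with it.

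**Step 4: simulation.** Twelve centres, about 500 patients, least squares with and without centre. At ICC 0.20 the mean SE was 1.50 without centre and 1.36 with it. Rejection under the null was 2.9% and 5.2%, and power 92.9% and 95.3%. At ICC 0.10 null rejection was noisier: 4.8% against 5.7% with equal centres and 3.4% against 4.2% with unequal ones. The individual rates scatter around the formula, but the model without centre rejected less often in both. Mean SEs there (1.51 and 1.44) agree with the table.

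**The case against.** The strongest reply is that this is a condensed article. The sentence on the model explains how the factorial structure is handled, the word introducing the terms does not close the list, and adjustment for stratification factors is often left to the full protocol or the analysis plan. Part of this stands: the article does not say that centre is excluded, and a fuller document may add it. But the article goes beyond a general statement. It names the covariate and even a conditional term, and leaves out the one factor used to stratify. As written, that model does not match the design.

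The second reply is that little is lost, and this stands. The consequence depends on an ICC that the documents do not give. At 0.02 or below it is negligible, and the larger figures come only from the top of the assumed range.

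Three stronger readings are tempting and should be resisted:
- A reader might infer that the trial is underpowered for CCF. It is not. Power without centre is at least 90.8% at the planned size for every ICC examined, and it rises with ICC.
- A reader might infer that power is lost in both primary comparisons. For CCS, at the planned 15-point difference, power exceeds 99% either way.
- A reader might infer a biased estimate or an inflated false-positive rate. The error runs the other way: the test is conservative.

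**Conclusion.** The point holds as a free improvement with a modest gain. The stated model omits the stratification factor, and if CCF or CCS varies between centres its standard errors are overstated. That they are overstated is conditional, because the documents give no between-centre variance.

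Under the assumed ICCs the excess in the CCF standard error runs from nothing at 0 to about 12% at 0.20, with a power difference from 0 to 2.6 points. At an ICC of 0.05 or less it is at most 2.6% and under 1 point. For CCS the benefit is narrower intervals and a better calibrated test only.

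These figures assume near-complete balance within centres, the article's SDs as total SDs, and 250 analysed patients per margin. Exclusions after randomisation would reduce the last. As an illustration, with 225 per margin (an assumed 10% loss) and ICC 0.10, the formulas above give CCF power of Φ[(5/1.603 − 1.960)/0.949], about 89%, without centre. With centre they give Φ(5/1.521 − 1.960), about 91%.

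**What to change.** Add centre, as the stratification factor, to the prespecified primary models for both CCF and CCS. A fixed effect is enough if centres recruit reasonable numbers (500/12 is about 42 each on average). A random intercept is the alternative if some recruit few. State which will be used before the data are analysed. Carry the same term into the sensitivity analyses, including the full intention-to-treat analysis with multiple imputation. If the full protocol or analysis plan already includes centre, it is enough to confirm this.

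The cost is one phrase in the plan and, with fixed effects, 12 − 1 = 11 degrees of freedom out of about 490. No new data, change in conduct or change in sample size is needed.
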